## Abstract

**Background:**

To compare the success and safety of microcatheter-assisted 360° trabeculotomy (MCAT) with conventional probe trabeculotomy in a large, heterogeneous cohort of children with primary or secondary glaucoma.

**Methods:**

In this prospective, multicenter, observer-blinded, randomized controlled trial, 76 children (152 eyes) with bilateral primary or secondary childhood glaucoma aged ≤ 12 years will be included. Each child acts as own control using a paired-eye design: One eye is allocated to MCAT (experimental intervention), achieving a 360° trabeculotomy, the other eye to the probe trabeculotomy (control intervention) which enables a trabeculotomy over 90 to 120°. Each child receives both procedures (paired-eye design). The worse eye is treated first; the surgical method is randomized. Patients and observers are masked to the procedures. The patients are followed up for 24 months. The primary endpoint is complete success (IOP < 18 mmHg at 24 months without medication and revision surgery; with MCAT: successful probing of > 120° is also required for success) at 24 months of follow-up. The primary analysis is performed in the intention-to-treat population using McNemar test stratified by center.

**Discussion:**

The PIRATE study is a multicenter randomized controlled study comparing MCAT with conventional probe trabeculotomy in a large and heterogeneous childhood glaucoma population. It will provide data on the success and safety of both techniques and clarify if MCAT is superior to probe trabeculotomy.

**Trial registration:**

German Clinical Trials Register, DRKS-ID: DRKS00034139. Registered on April 24, 2024. https://drks.de/search/en/trial/DRKS00034139. https://trialsearch.who.int/Trial2.aspx?TrialID=DRKS00034139.

**Supplementary Information:**

The online version contains supplementary material available at 10.1186/s13063-025-09091-3.

## Background

Childhood glaucoma leads to loss of visual function if not treated. The cause is high intraocular pressure (IOP) due to a dysgenesis of the outflow pathway of the aqueous humor. Most cases of congenital glaucoma need surgery [1–3]. Trabeculotomy, which opens Schlemm’s canal and therewith the eye’s drainage system, is the most common surgical intervention and is considered the gold standard [3–6]. In conventional probe trabeculotomy, bowed metal probes are inserted ab externo into the Schlemm’s canal, which is opened by rotating the probe into the anterior chamber [7]. The 1-year success rates of conventional trabeculotomy in primary congenital glaucoma vary from 47% to over 92% depending on glaucoma severity and kind of glaucoma [8, 9]. A second and newer approach is circumferential trabeculotomy, using an illuminated microcatheter for dilatation and opening the Schlemm’s canal over 360°. A circumferential opening of Schlemm’s canal may theoretically lead to a better IOP decrease than a partial opening as performed in probe trabeculotomy.

At the present time, two prospective randomized controlled studies comparing microcatheter-assisted trabeculotomy (MCAT) with conventional probe trabeculotomy [8, 10] have been published. El Sayed and Gawdat reported a complete success (defined as IOP < 18 mmHg, no other signs of glaucoma progression, no antiglaucoma medications) of 67% versus 47% for MCAT compared to conventional probe trabeculotomy after 2-year follow-up in a sample with 62 Egyptian patients (62 eyes) with primary congenital glaucoma [8]. Shakrawal et al. achieved 1-year complete success in 80% versus 60% with stricter criteria for complete success (IOP ≤ 12 mmHg, no antiglaucoma medications) in a sample with 31 Indian patients (40 eyes) with primary congenital glaucoma [10].

The largest retrospective study performed by Berger et al. showed higher complete surgical success (69% versus 23%, *p* < 0.0001) with significantly lower revision rates after MCAT than after conventional trabeculotomy with a rigid probe in 77 children (106 eyes) with glaucoma [11].

Two systematic reviews with meta-analyses (Ling et al. also included three retrospective studies in addition to the two RCTs) showed a lower IOP and a higher probability for complete and qualified success for MCAT than for probe trabeculotomy, but also a higher risk for the occurrence of hyphema [12, 13]. However, there was a high heterogeneity in the intervention groups and a high probability of performance and observation bias due to lack of masking [12, 13].

Although various attempts have been made to evaluate the efficacy and safety of MCAT compared to probe trabeculotomy, sample sizes and the trial quality are low. Only two randomized controlled studies are available, which comprised Egyptian and Indian patients. Furthermore, most trials did not include secondary glaucoma patients. Thus, there is an unmet need for a large-scale, multicenter prospective randomized controlled trial investigating a real-life childhood glaucoma population. The researchers expect similar results as shown in the aforementioned previous studies, with superiority of 360° trabeculotomy compared to conventional probe trabeculotomy (TO). The results of a larger scaled study will contribute to the acceptance of MCAT as a standard therapy for both primary and secondary childhood glaucoma patients.

## Methods

### Aim, design and study setting

The aim of this study is to compare microcatheter-assisted 360° trabeculotomy with conventional probe trabeculotomy in children aged ≤ 12 years with primary or secondary glaucoma.

The primary hypothesis of this study is that MCAT is superior to probe trabeculotomy with respect to complete success at 24 months after surgery. The key secondary hypothesis is that MCAT is superior to probe trabeculotomy with respect to incomplete success at 24 months after surgery. Further secondary hypotheses address the superiority of MCAT with respect to complete and incomplete success at earlier time points and the superiority of MCAT with respect to other clinical parameters.

Four academic centers are contributing to the study. The coordinating center is the Department of Ophthalmology, University Medical Center Mainz (Germany), which is an academic hospital. Further centers are the Department of Ophthalmology, University Clinic Cologne (Germany), the Department of Ophthalmology, University Hospital Magdeburg (Germany), and the Department of Ophthalmology, UZ Leuven (Belgium).

A paired-eye design is used: each patient receives both interventions (experimental intervention in one eye and control intervention in the other eye in randomized sequence) and acts as his or her own control thus minimizing the influence of external factors on the outcome and the case numbers. The worse affected eye (i.e., higher IOP, longer axial length, greater corneal diameters, and greater cup-to-disc ratio) will be treated first; the investigator assesses which eye is worse affected.

To prevent selection bias, intervention sequence (probe TO, MCAT) will be randomized. Block randomization will be applied using variable block length and stratification by center. Sealed numbered envelopes generated by the coordinating center are provided containing which surgical technique must be used on the first and second eye, respectively.

To prevent observation bias, an independent observer masked to the intervention and not involved in the surgery will conduct the follow-up visits. At the slit lamp, a morphological differentiation between MCAT and probe TO is not possible and postsurgical treatments are the same after both procedures, so making this easily possible. Furthermore, patients, their parents, and their treating pediatricians and ophthalmologists are also masked to the intervention.

The patients will be followed up for 24 months. Six follow-up visits are planned (after 1, 3, 6, 12, 18, and 24 months), where the 3-month follow-up visit is optional. The follow-up visits adhere to the standard of clinical care and are well accepted by the patients and caregivers. Thus, complete follow-up is very likely. Additional examinations, which will be performed for a clinical reason, will also be documented. Examinations take place either in awake setting or under general anesthesia (examination under anesthesia, EUA), depending on the cooperation of the child and on the discretion of the observer. The full study schedule is presented in Fig. 1. In case of withdrawal from the study, an end-of-trial examination is performed.

**Fig. 1 Fig1:**
[figure not shown]
SPIRIT figure presenting the time schedule of enrollment, interventions, and assessments. Additional visits for clinical reasons will also be documented. Abbreviations: IOP, intraocular pressure; EUA, examination under anesthesia; AE, adverse event. ^1^Bilateral surgery should be preferred if clinically feasible; if not, sequential surgery can be performed. ^2^Visit 1 and follow-up visits refer to the date of surgery per eye

An interim analysis will be conducted when 38 patients (half of the initially planned sample) have had their 6-month follow-up visit. The interim analysis is conducted because the correlation between the successes of the two eyes of a patient is unknown. The interim analysis to be performed by the data safety monitoring board (DSMB) only has the aim to obtain a better proxy of the correlation and hence the proportion of discordant pairs which impact the required sample size for the desired significance level and power. Simulations performed by one of the study statisticians indicate that the significance level of the final analysis will be kept after this interim analysis. As the primary endpoint will be determined 2 years after treatment, the only possible change in study design is an increase in sample size (up to a maximum of 83 rather than 76). Neither stop for futility nor early stop for success is planned.

### Participants

One hundred fifty-two eyes of 76 children with bilateral primary or secondary childhood glaucoma will be included. Inclusion and exclusion criteria are as follows:Inclusion criteriaAbility of participant’s legal representatives to understand nature, importance, and individual consequences of clinical trial.Signed and dated informed consent of legal representatives and children, if applicable, must be available before start of any specific trial procedures. Both caregivers must sign the informed consent.Patients with primary congenital or different types of secondary childhood glaucoma at age ≤ 12 years with both eyes requiring trabeculotomy and no other previous glaucoma surgeries.Exclusion criteriaIndication other than trabeculotomy, e.g., glaucoma drainage device implantation or cyclodestructive treatmentPrior glaucoma surgery (other surgeries, such as lensectomy or vitrectomy, are allowed)Language barrierMedical or psychological conditions that would jeopardize an adequate and orderly completion of the trial

### Interventions

#### Microcatheter-assisted 360° trabeculotomy (MCAT)

A limbal-based conjunctival peritomy at 6 mm from the limbus is performed. Then, a partial-thickness scleral flap of size 4 × 4 mm is created. The second, deep scleral flap of size 1.5 × 3 mm is created within the borders of the superficial flap dissecting forward, exposing the choroid, into clear cornea. The roof of Schlemm’s canal (SC) is carefully detached with multifunctional 25-gauge forceps. Then, insertion of an illuminated microcatheter is performed over 360°. Every 60°, viscoelastic is injected into SC via the screw-driven injector. The optical fiber that illuminates the tip of the microcatheter provides guidance to the path of the catheter as it is advanced. Care is taken to keep the catheter in perpetual motion through SC when viscoelastic is injected to prevent the creation of a Descemet’s membrane detachment. When the distal tip of the catheter re-emerges from the opposite opening of SC, a paracentesis wound is created with a 15-degree side port knife at the temporal clear cornea. Acetylcholine chloride intraocular solution is given to constrict the pupil. Viscoelastic to protect lens and endothelium is injected. Then, both ends of the catheter are pulled to create a circumferential rupture of the trabecular meshwork (TM). If probing over 360° is not possible, a scleral incision at the site of the catheter’s tip is performed and the catheter is emerged at this point, and the catheter ends are pulled to create the TM rupture (probing of at least 120° is necessary to successfully conduct the rupturing). The scleral flap and conjunctiva are sutured tightly and viscoelastic is removed from the anterior chamber. Subconjunctival injection of 4 mg dexamethasone is performed in the inferior fornix of the conjunctiva, and then antibiotic ointment is applied prior to bandage.

#### Conventional probe trabeculotomy

Similar opening for both surgeries. After de-roofing of SC, a paracentesis is created with a 15-degree side port knife at the temporal clear cornea. Then, insertion of right and left trabeculotomy probes into SC is performed to open its inner wall over 90–120°. The scleral flap and conjunctiva are sutured tightly and viscoelastic is removed from the anterior chamber. Subconjunctival injection of 4 mg dexamethasone is performed in the inferior fornix of the conjunctiva, and then antibiotic ointment is applied prior to bandage.

#### Postoperative medications

Postoperative topical medications for both surgical methods include topical dexamethasone and topical antibiotic therapies. The choice of substance and dosage is at the discretion of the surgeon. Furthermore, pilocarpine eye drops can be prescribed at the discretion of the surgeon.

In cases of transient hypotony with anterior chamber shallowing, atropine may be prescribed.

#### Emergency treatment

Topical antiglaucomatous medication (eye drops), such as timolol, latanoprost, and dorzolamideSystemic antiglaucomatous medication: acetazolamide (per os/intravitreal), osmotic substances (e.g., mannitol)IOP-lowering procedures: angle surgery (any type of re-trabeculotomy), glaucoma drainage implants, cyclophoto-/cyclocryocoagulation, trabeculectomy

#### Post-trial care

After completing the trial, the participants will be treated and followed up according to the clinical standards which rely on the current recommendations of the medical societies for pediatric glaucoma (e.g., European Glaucoma Society, UK Pediatric Glaucoma Society). An insurance covering study-associated harms will be provided.

### Sample size

El Sayed and Gawdat [8] observed 14 complete successes in 30 eyes at 2 years (47%) treated conventionally and 18 complete successes in 29 eyes treated with MCAT (62%—counting as failures those eyes in which less than 120° was possible). Therefore, we also aim to establish a difference in success rates of 15% at the 5% significance level with 80% power. In our previous experience, at most 20% of outcomes differ between both eyes of a patient. Therefore, we assume that the proportion of discordant pairs (i.e., success only with one technique in a patient) is 20%. This is equivalent to a correlation of 0.63 given overall probabilities of success of 47% and 62%.Power calculation has been performed using SAS PROC power. We found that with 72 patients and a correlation of 0.63 between eyes there is 80% power to detect an increase from 47% success rate to 62% success rates at the 5% level.We assume a dropout rate of 5% due to the empirically excellent adherence of the patients. Therefore, 76 patients are to be randomized in this study. The expected CONSORT flow diagram is presented in Fig. 2.

**Fig. 2 Fig2:**
[figure not shown]
CONSORT flow diagram with expected case numbers

### Recruitment

Patients will be recruited from the childhood glaucoma consultation hours in each study center. A flyer will be provided to improve the interest in the study. A self-aid group (Bundesverband Glaukom-Selbsthilfe e.V.) has been involved in the study design and in disseminating the initiation of the study. Furthermore, recruitment of more study centers can be performed in case of low recruitment numbers.

### Interim analysis

One interim analysis of the primary endpoint is planned after 50% of the patients have completed their 6-month follow-up. As there is little previous knowledge about the correlation of outcomes, and consequently about the proportion of discordant pairs, sample size may be re-calculated after 50% of the patients have completed their 6-month follow-up.

The DSMB will evaluate the proportion of discordant pairs at 6 months. No further information on interim results shall be disclosed, thus retaining the integrity of the trial. This proportion will be taken as a proxy for the proportion of discordant pairs at 24 months, and sample size may be increased if the proportion of discordant pairs at 6 months is substantially different from 20%. The sample size may be increased up to 83 participants depending on the proportion of discordant pairs such that—given the unchanged assumption of a 15% difference—there is still 80% power to establish a 15% difference in success probability at the 5% significance level.

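### The capped sample-size re-estimation states that 80% power is retained, but with the calculation that reproduces the planned 72 pairs, 83 children hold 80% only up to about 22–23% discordant pairs

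*Protocol article*

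**What the plan says.** The Sample size section sets the target: "we also aim to establish a difference in success rates of 15% at the 5% significance level with 80% power". It assumes 20% discordant pairs, on the ground that "In our previous experience, at most 20% of outcomes differ between both eyes of a patient". It concludes that 72 pairs give "80% power to detect an increase from 47% success rate to 62% success rates at the 5% level", and 5% dropout raises 72 to 76 randomised.

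The Interim analysis section concedes that little is known about the correlation between eyes. The monitoring board looks at the proportion of discordant pairs once half the children (38) have reached 6 months. If that proportion departs substantially from 20%, the number may be raised: "The sample size may be increased up to 83 participants depending on the proportion of discordant pairs such that" (with the 15-point difference kept) "there is still 80% power to establish a 15% difference in success probability at the 5% significance level". No number defines a substantial departure.

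The interim paragraph below Fig. 1 makes the ceiling firm: "the only possible change in study design is an increase in sample size (up to a maximum of 83 rather than 76"). Neither place gives the range of discordance that 83 children cover, or says that power drops beyond it.

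**The concern.** For a fixed 15-point difference, the power of McNemar's test falls as the proportion of discordant pairs rises. The interim look exists because that proportion is uncertain. Moving from 76 to 83 adds only 7 children, about 9%, so it can offset only a small rise in discordance. The text nevertheless presents 80% power as the result of the adaptation.

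What is at stake is how a non-significant result would be read. If discordance proves to be 25–30%, readers would take the trial as having 80% power for 15 points when it had clearly less. The type I error rate, the estimand and the conduct of the trial are not affected.

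**Working it through.** **Inputs (protocol article).** Success 47% and 62%, difference 0.15, level 5%, power 80%, discordance 20%, correlation 0.63, 72 evaluable, 5% dropout, 76 randomised (Sample size). Cap 83 and interim size 38 (interim paragraph below Fig. 1). McNemar's test (Primary outcome).

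**Formula.** Let ψ be the proportion of discordant pairs. The two discordant cells are (ψ + 0.15)/2 and (ψ − 0.15)/2. The number of discordant pairs M is Binomial(n, ψ). Given M, the number favouring MCAT is Binomial(M, q) with q = (ψ + 0.15)/(2ψ). Power is the probability of rejection by the two-sided exact binomial test of q = 0.5 at 5%, averaged over M.

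**Step 1: reproduce the plan.** At ψ = 0.20 the cells are 0.175 and 0.025, and q = 0.875. The both-success cell is (0.47 + 0.62 − 0.20)/2 = 0.445. The correlation is (0.445 − 0.62 × 0.47)/√(0.62 × 0.38 × 0.47 × 0.53) = 0.634, which agrees with 0.63. Power is 79.9% with 71 pairs and 80.6% with 72. At correlation 0.63 exactly (ψ = 0.202), 72 pairs give 80.0%. Then 72/0.95 = 75.8, so 76. The plan's figure is reproduced.

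Other two-sided methods at ψ = 0.20 give 73 (continuity-corrected), 68 (Connor), 62 (asymptotic McNemar) and 60 (Miettinen). Only the exact and, within one pair, the continuity-corrected test match 72.

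**Step 2: apply the same calculation to the cap.** 83 × 0.95 = 78.85, about 79 evaluable. If no information is lost, 83 are evaluable.

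| Discordance | Evaluable needed for 80% | Randomised (÷ 0.95) | Power, 79 evaluable | Power, 83 evaluable |
|---|---|---|---|---|
| 20% | 72 | 76 | 85.0% | 87.1% |
| 8/38 = 21.1% | 76 | 80 | 82.4% | 84.6% |
| 22% | 79 | about 83 | 80.1% | 82.4% |
| 23% | 83 | 88 | 77.7% | 80.1% |
| 9/38 = 23.7% | 86 | 91 | 76.1% | 78.5% |
| 25% | 92 | 97 | 73.1% | 75.4% |
| 30% | 112 | 118 | 62.8% | 65.3% |

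The discordance at which power falls to 80% is 22.0% with 79 evaluable and 23.0% with 83.

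**Step 3: compare with the interim resolution.** One child in 38 is 1/38 = 2.6 points. Under the exact test, 8/38 is inside the limit and 9/38 is outside it, whichever evaluable number is used.

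**Step 4: vary the test.** Limits for 79 / 83 evaluable: continuity-corrected 21.4% / 22.3%; Connor 23.3% / 24.5%; Miettinen 25.0% / 26.0%; asymptotic McNemar 25.2% / 26.5%. Every two-sided variant falls below 80% by 27% discordance.

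**The case against.** **The wording is permissive and the cap is disclosed.** The number may be increased, and the ceiling of 83 stands in the same sentence as the power statement. One can read this as aiming at 80% within the cap. A feasibility cap in a rare disease is also legitimate. Both points are fair, but the sentence gives 80% power as the outcome of the increase, and nothing says that it ceases to hold when the cap binds.

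**The final test is not fixed as exact.** The plan names McNemar's test stratified by center. With an asymptotic test, 9/38 is within the cap (82.8% power with 79 evaluable), and with 83 evaluable so is 10/38 (80.3%). This stands, and the limit must be tied to the test. But the asymptotic test needs only 62 pairs at 20%, so it is not the calculation behind 72.

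**Multiple imputation keeps all randomised children in the analysis.** If it recovered all the information, the limit would be 23.0%. That is optimistic, since the plan itself inflates for dropout, but a range is the honest statement.

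**Stronger readings that the documents do not support:**
- *The margin is less than one child.* It is 0.77 child in 38 with 79 evaluable (0.22 × 38 − 7.6 is about 0.77), but 1.15 with 83, and wider with an asymptotic test.
- *The trial will often lose power even if discordance is truly 20%.* A count of 9 or more in 38 then has probability 34%, but enrolling 83 would give true power of 85–87%. The figure shows noise in the interim estimate only.
- *A low interim count makes the 15-point difference impossible.* The 6-month proportion is only a proxy with sampling error, and a low value calls for no increase.
- *The prior 20% comes from eyes treated with the same technique, so true discordance must be higher.* The text does not say which eyes the experience concerns.

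**Conclusion.** The statement of retained power is wrong as written. Under the exact two-sided calculation that reproduces 72 pairs, the cap of 83 covers discordance only up to 22% (5% dropout) or 23% (no loss), that is, 2 to 3 points above the planning value. Beyond that, power is 76–78% at 9/38, 73–75% at 25% and 63–65% at 30%. An upward departure that could reasonably be called substantial lies outside this range, and a downward one needs no increase.

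The result assumes a true 15-point difference, a two-sided 5% level, no modelling of the center strata, and a 6-month proportion that carries over to 24 months. With the asymptotic test the limit moves to about 25–26.5%.

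This is a misstatement of power that should be corrected. It does not show that the trial is underpowered at its planning assumption of 20%, where 72 evaluable pairs do give 80%.

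**What to change.** In the Interim analysis section and in the interim paragraph below Fig. 1, replace the retained-power statement with text such as:

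> An increase to at most 83 randomised children keeps 80% power for a 15-point difference only if the proportion of discordant pairs does not exceed about 22% (79 evaluable) to 23% (83 evaluable), under the exact McNemar test used for planning. With 83 randomised, power is 73–75% at 25% discordance and 63–65% at 30%. A proportion of 20% or less leads to no change in sample size.

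The trial statisticians should confirm that the exact test was the planning method. If the final analysis will use an asymptotic test, they should give the corresponding limit, about 25–26.5%.

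The cost is a wording change in the protocol and the matching place in the statistical analysis plan. No extra patients are needed and the primary test need not change. The published power statement becomes less favourable.
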